### 2.7 Criteria for discontinuing or modifying allocated interventions

If a severe or unanticipated adverse event that may influence the risk-benefit ratio of the study occurs, the principal investigator must report to the ethics committee and permanently discontinue the treatment. Peking University Third Hospital, the sponsor of this study, will pay for medical expenses and provide economic compensation for the injuries related to this study. Study treatment must be stopped permanently in the event of unintended pregnancies. In addition, participants can withdraw from the trial at any stage for any reason. For patients with limited symptom response, we will provide alternative interventions including switching medication, probiotics and dietary guidance.

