**FIGURE 1 F1:**
[figure not shown]
Flow diagram based on the Consolidated Standards of Reporting Trials guidelines (CONSORT): Neg, negative; CRF, case report form.

Before LHMBT, all subjects are supposed to refrain from antibiotic use and discontinue probiotics, laxatives, antidiarrheal and prokinetic agents for 2 weeks. To minimize basal hydrogen excretion, dietary restriction and avoidance of smoking for at least 24 h prior to the test and during the test are recommended. Furthermore, patients are required to avoid coarse grains, milk, juice, and alcohol in the evening before the test. Fasting for 8–12 h before the procedure is needed. Before the examination, subjects use 20 mL antiseptic mouthwash (0.05% chlorhexidine) to eliminate fermentation by oral bacteria. End-expiratory breath samples will be collected just before the ingestion of 10 g (15 mL) of lactulose in a 250 mL water solution. Gas samples are collected every 15 min until 90 min and tested immediately by the methane-hydrogen breathing analyzer DA6000 (Sunvou Medical Electronics Co., Ltd., Wuxi, China). A rise in hydrogen of ≥20 part per million (ppm) by 90 min with elevated or normal methane was considered positive. Patients with only methane levels ≥10 ppm are not eligible (Rezaie et al., 2017).

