#### 2.3.2 Intervention

In total, 180 patients will be recruited and divided into two groups: the berberine group (Berberine Hydrochloride Tablets, H51022193, Chengdu Jinhua Pharmaceutical Co., Ltd., China) and the rifaximin group (Xifaxan, H20181212, Alfasigma S.p.A, Italy). Each participant will receive only one 400 mg drug twice a day (800 mg daily) for 2 weeks. The recommended dose of berberine is mainly determined by the advice of pharmacological experts, while that of rifaximin is based on past clinical trial conclusions. The first participant was enrolled on 15 March, 2022, and the study is expected to be terminated by July 2023 with the anticipated inclusion of 180 participants.

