#### 2.3.3 Follow-up

The total follow-up period is 6 weeks from the start of medication. Efficacy assessment will be performed every 2 weeks using GSRS (Dimenäs et al., 1993), Bristol Stool Form (BSF) and breath tests, as well as safety assessment during the first 2 weeks of treatment. Each specific visit and measurement are summarized in Table 1. Multiple methods, such as telephone and online follow-up, are carried out to improve patient compliance if room consultation is impossible. Participants will return unused tablets and report reasons for non-compliance at the first visit (Kini and Ho, 2018). If a patient decides to withdraw, the follow-up will be stopped.

**TABLE 1 T1:** Standard protocol items: Adapted recommendations for interventional trials (SPIRIT) schedule: Enrollment, interventions, and follow-up.

	Screening	1 week	2 weeks	4 weeks	6 weeks
Case report form	×				
GSRS and BSF	×		×	×	×
Breath test	×		×	×	×
Blood test	×				
Enteroscopy	×				
Stool 16S rRNA sequencing	×		×	×	×
Medication record		×	×		
Adverse event		×	×		

Legend: GSRS, gastrointestinal symptom rating scale; BSF, bristol stool form.

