### 2.4 Results

#### 2.4.1 Effectiveness outcomes

The primary outcome is a negative LHMBT. It is defined as a rise of hydrogen less than 20 ppm and methane less than 10 ppm within 90 min compared with screening tests.

The secondary outcomes include abdominal symptom relief and alterations in gut microbiota. The key secondary outcome we designed was similar to the relief of IBS global symptoms (Pimentel et al., 2011). Abdominal symptom remission is required to meet at least one of the following criteria: 1) The pain or distension scores of GSRS decrease at least 30% from baseline; 2) Hard stool (1/2 in BSF) and loose stool (6/7 in BSF) reduce more than 50% from baseline.

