### 2.5 Randomization and allocation

Participants will be randomized after baseline assessment to either berberine or rifaximin intervention with a 1:1 allocation. A laboratory staff member, not the investigator, used Statistical Package for Social Science Version 26.0 software (SPSS V.26.0) to produce 180 random numbers after setting the starting point according to the simple randomization. The patient codes were divided into two groups (A for berberine and B for rifaximin) according to the size of the number to form a random allocation table. The corresponding information of each code was assembled into the envelope seal. Thus, the principal investigator will remain blinded to the randomization process. Participants will be aware of the group to which they are allocated.

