### 2.8 Data management

The original data will be correctly, completely and clearly recorded in the written case report form and observation questionnaire. After being reviewed and signed by the principal investigator, the records should be sent in a timely manner to the clinical research data manager. The Microsoft Excel database will be used by two-person and two-machine input for checking. Data review will be performed regularly by the study monitoring committee to ensure completeness and accuracy. The monitor will finish a data inspection report for each participant, including the study completion, inclusion and exclusion criteria, pharmaceutical compliance, concomitant medication, adverse events, *etc.* During this period, the investigator should be required to answer if any problem is found, and the monitor will be informed in time. The exchange of questions and answers between them should be sent in the form of a question sheet for future reference.

The losses and dropouts will be carefully recorded to ensure study reliability. The next participant who meets the eligibility criteria will replace the last participant who withdraws from the research until reaching the calculated sample size. All participant information will be stored in a safe place anonymously by the responsible researcher as required by Chinese relevant laws to guarantee the security of privacy. The study results will be disseminated in a peer-reviewed journal and at conferences without any privacy information of participants.

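### Undated rescue for poor symptom response, with no primary LHMBT visit named, lets week-4/6 results mix two treatments and lets the per-protocol set select on response

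*Protocol article*

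**What the plan says.** All references are to the protocol article.

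- **Rescue (section 2.7).** "For patients with limited symptom response, we will provide alternative interventions including switching medication, probiotics and dietary guidance". No day, visit or response threshold is attached.
- **Treatment (section 2.3.2).** "Each participant will receive only one 400 mg drug twice a day", for 2 weeks.
- **Assessments (section 2.3.3 and Table 1).** "The total follow-up period is 6 weeks from the start of medication", and "Efficacy assessment will be performed every 2 weeks using GSRS", stool form and breath tests. Table 1 places GSRS/BSF, breath test and stool 16S sequencing at weeks 2, 4 and 6. It schedules the medication record at weeks 1 and 2 only.
- **Primary outcome (section 2.4.1).** "The primary outcome is a negative LHMBT". The 90 minutes in its definition is the test window, not a visit.
- **Key secondary outcome (section 2.4.1).** Abdominal symptom remission, based on GSRS and stool form.
- **Blinding (section 2.5).** "Participants will be aware of the group to which they are allocated".
- **Analysis sets (section 2.9).** The full analysis set (FAS) is primary and follows the ITT principle. The per-protocol set (PPS) is secondary and requires that no other treatment affecting the result was given in the course of the trial.

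**The concern.** Rescue is triggered by poor symptom response, and symptom response is the key secondary outcome. A patient switched after week 2 who feels better at week 4 or 6 would count, under ITT, as a success of the drug that failed. Stool samples taken after a second drug or a probiotic no longer describe the randomised drug, yet the microbiota comparison is meant to help explain how the two drugs differ.

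The same applies to LHMBT at weeks 4 and 6. If one of those tests were the primary outcome, rescue could move the berberine–rifaximin difference in a non-inferiority trial. Patients know their arm and the trigger is a symptom report, so equal switching rates are not assured.

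The PPS is not a dependable cross-check. Removing patients because they were rescued removes them by response.

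**Working it through.** **1. Order of events.** Study drug ends at week 2. The first post-baseline GSRS is at the same visit as the first post-baseline LHMBT. A switch based on scheduled symptom scores would therefore normally follow the week-2 LHMBT and fall before the week-4 and week-6 tests. Section 2.7 does not exclude an earlier switch.

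**2. Which results are exposed.**
- Week-2 LHMBT in the FAS: untouched if it precedes rescue.
- Week-4/6 LHMBT, symptoms and stool: exposed whichever visit is primary.
- Week-2 LHMBT in the PPS: exposed, because the exclusion refers to the whole trial and not to the period up to the test.

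**3. Illustration for the FAS, if a post-rescue LHMBT were analysed.** The article gives no switch rate or rescue success, so it has no figure of its own to reproduce here. From section 2.6 I take the rifaximin rate, pR = 72.9%. I assume a true berberine rate of pB = 57.9%, a 15.0-point deficit. Let u be the share of breath-test failures that rescue turns negative (assumed).

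Observed rate: p' = p + (1 − p)u. 
Observed gap: (pR − pB) + (1 − pR)uR − (1 − pB)uB, with 1 − pR = 0.271 and 1 − pB = 0.421.

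| uB | uR | berberine | rifaximin | gap (points) |
|---|---|---|---|---|
| 0 | 0 | 57.9 | 72.9 | 15.0 |
| 0.05 | 0.05 | 60.0 | 74.25 | 14.25 |
| 0.10 | 0.10 | 62.1 | 75.6 | 13.5 |
| 0.10 | 0.05 | 62.1 | 74.25 | 12.1 |
| 0.05 | 0.10 | 60.0 | 75.6 | 15.6 |
| 0.25 × 0.729 | 0.25 × 0.579 | 65.6 | 76.8 | 11.25 |

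In the last row, 25% of failures cross to the other study drug and clear at its rate. The gap shrinks only while uR/uB < (1 − pB)/(1 − pR) = 0.421/0.271 = 1.55. At the planned rates of 69.8% and 72.9% the limit is 0.302/0.271 = 1.11.

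**4. Illustration for the PPS.** If a share s of breath-test failures is dropped (assumed), p' = p/[p + (1 − p)(1 − s)].

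| sB | sR | berberine | rifaximin | gap (points) |
|---|---|---|---|---|
| 0.25 | 0.25 | 64.7 | 78.2 | 13.5 |
| 0.25 | 0.10 | 64.7 | 74.9 | 10.2 |
| 0.10 | 0.25 | 60.4 | 78.2 | 17.75 |

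The same 15.0-point deficit can look smaller or larger. The article states no non-inferiority margin, so I do not convert these gaps into error rates.

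**The case against.** **Week 2 is the obvious primary visit.** One drug is given for 2 weeks and the abstract speaks of the effect of 2 weeks of treatment. This stands. A reader might infer that the primary FAS result is biased, or biased towards false non-inferiority. The documents do not support that: the harm needs a later primary visit or earlier rescue, and even then the direction is open.

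**The washout rule.** A reader might also infer that rescue started at week 2 breaks the breath-test preparation rule: "Before LHMBT, all subjects are supposed to refrain from antibiotic use and discontinue probiotics, laxatives, antidiarrheal and prokinetic agents for 2 weeks". That does not hold. The rule sits in section 2.3.1, Screening. Applied literally to follow-up, it would bar the week-2 test in the rifaximin arm, which comes straight after 2 weeks of an antibiotic.

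**The figures model the wrong trigger.** Rescue follows symptoms, not the breath test, and the article gives no link between the two. If switching were unrelated to the breath result within each arm, dropping switchers would leave the PPS rates for LHMBT unchanged. The shifts can also be small: 0.75 to 1.5 points at u = 5% to 10% in both arms, against a standard error of √[(0.729 × 0.271 + 0.579 × 0.421)/82] = 7.3 points with 82 per arm. This stands, so the tables show possibility only.

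**This is detail for the full protocol or SAP.** In part. Silence about post-rescue data would not by itself be a finding in a journal article. But the rescue offer and the PPS exclusion are stated rules that work badly together, and the primary visit is a core protocol item.

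**The PPS wording is unclear.** True. It does not say that alternatives offered by the protocol count as other treatments, and dietary guidance might not. A medication switch or a probiotic is hard to read otherwise.

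**Switchers might be treated as withdrawn.** The article does not say so. Section 2.3.3 stops follow-up only when a patient decides to withdraw, and section 2.8 would then replace that patient, which again selects on response.

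**Conclusion.** The point holds in a limited form and should be corrected; confidence is medium. As written, week-4/6 symptom, LHMBT and microbiota results can mix the randomised drug with a second treatment. On its natural reading, the PPS rule removes patients by symptom response even from a week-2 comparison completed before rescue.

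The effect on the primary FAS result is nil if the week-2 LHMBT is primary and rescue follows it. Otherwise direction and size cannot be determined from the article. The illustrated gaps (11.25 to 15.6 points in the FAS and 10.2 to 17.75 in the PPS, for a true 15.0) rest wholly on an assumed deficit, assumed rescue or exclusion shares, and a breath-test trigger in place of the symptom trigger that the article states.

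**What to change.** - **Section 2.4.1:** name the week-2, end-of-treatment LHMBT as primary.
- **Section 2.7:** start alternative interventions for limited symptom response only after the week-2 LHMBT, GSRS/BSF and stool sample have been taken. Care for adverse events stays as it is.
- **Data collection:** record the type and start date of any alternative treatment through week 6. The monitor's report already covers "pharmaceutical compliance, concomitant medication, adverse events" (section 2.8), so the addition is mainly dates after week 2.
- **Section 2.9, PPS:** for the week-2 outcome, define the set by treatments received up to that test only.
- **Week-4/6 symptom remission:** count patients switched for poor symptom response as non-responders.
- **Week-4/6 LHMBT and stool:** flag post-switch samples and keep them, with a sensitivity analysis. For LHMBT, that analysis should give no credit for a negative first obtained after a switch, and should not recode patients who were already negative before it.

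Cost: a few lines of text, a short delay before rescue for some patients (a small restriction on section 2.7), and slightly lower reported week-4/6 response rates.

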### 2.8 Data management

The original data will be correctly, completely and clearly recorded in the written case report form and observation questionnaire. After being reviewed and signed by the principal investigator, the records should be sent in a timely manner to the clinical research data manager. The Microsoft Excel database will be used by two-person and two-machine input for checking. Data review will be performed regularly by the study monitoring committee to ensure completeness and accuracy. The monitor will finish a data inspection report for each participant, including the study completion, inclusion and exclusion criteria, pharmaceutical compliance, concomitant medication, adverse events, *etc.* During this period, the investigator should be required to answer if any problem is found, and the monitor will be informed in time. The exchange of questions and answers between them should be sent in the form of a question sheet for future reference.

The losses and dropouts will be carefully recorded to ensure study reliability. The next participant who meets the eligibility criteria will replace the last participant who withdraws from the research until reaching the calculated sample size. All participant information will be stored in a safe place anonymously by the responsible researcher as required by Chinese relevant laws to guarantee the security of privacy. The study results will be disseminated in a peer-reviewed journal and at conferences without any privacy information of participants.

### 2.9 Statistical analysis

Patients who finish at least one postmedication evaluation after randomization and subsequent treatment constitute the study full analysis set (FAS) as well as the primary group of efficacy assessment, according to the intention to treatment (ITT) principle. Patients who meet the criteria and complete the observation before medication without other affected treatments during the trial will be included in the study per protocol set (PPS) as the secondary group of efficacy assessment. The study safety set consists of all cases who have safety evaluation data after taking at least one kind of drug. Rubin’s method of multiple imputation will be performed for missing values to restore natural variability and uncertainty. The complete and imputed datasets will be combined and analyzed (Little et al., 2012). Complete case analysis is used for fecal microbiota on the nature of the outcome.

Analysis will be conducted using SPSS V.26.0. The quantitative and qualitative variables were reported as mean ± standard deviation (SD), median ± interquartile range (IQR), and number (frequency). Univariate analysis of variance (ANOVA) will examine differences between groups for variables with continuous data. χ2 tests will examine differences between groups for categorical variables. Unadjusted ANOVA and adjusted analysis of covariance models will compare differences in scores from baseline and postintervention data within and between groups using FAS and PPS. Variable correlations will be analyzed through Spearman’s correlation analysis. Statistical significance was defined as a *p*-value less than 0.05.

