#### 2.4.2 Assessment of harms

The study investigator will exclude those with any physical problems that may limit participation with berberine or rifaximin exposures. Participants will be asked to report any adverse events (AEs) experienced during the study period. Participants with adverse events (e.g., dizziness, headache, loss of taste, dull sensation, diplopia, vertigo, palpitations, hot flashes, dyspnea, hematochezia, rash, back pain, muscle spasm, muscle weakness, hematuria, fever, flu-like symptoms after intervention) will be advised to consult their physician to provide healthcare as appropriate. The investigator will record the details of the frequency and severity of adverse events.

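### The safety set requires post-dose safety data while withdrawal ends follow-up, so a dosed patient who leaves before week 1 without reporting an event can drop out of the adverse event comparison

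*Protocol article*

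**What the plan says.** Section 2.9 of the protocol article gives the rule: "The study safety set consists of all cases who have safety evaluation data after taking at least one kind of drug". A patient must meet two conditions to be counted: having taken drug, and having safety data afterwards.

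Section 2.3.3 describes safety monitoring "as well as safety assessment during the first 2 weeks of treatment". In Table 1 the row "Adverse event" carries two marks, at week 1 and week 2. The same section states: "If a patient decides to withdraw, the follow-up will be stopped". It makes no exception for safety information.

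Section 2.7 says that "participants can withdraw from the trial at any stage for any reason", which includes the days before week 1. Section 2.8 adds: "The next participant who meets the eligibility criteria will replace the last participant who withdraws from the research until reaching the calculated sample size".

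On the other side, section 2.4.2 provides for spontaneous reports: "Participants will be asked to report any adverse events (AEs) experienced during the study period". Section 2.3.3 also allows telephone and online contact when a visit in person is not possible.

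**The concern.** Having safety data is a post-randomisation event, and it can depend on how well the drug is tolerated. The first scheduled adverse event assessment is at week 1, and withdrawal ends contact. Someone who takes a few doses and leaves quietly may have no safety record at all, and the section 2.9 definition then removes that person from the analysis rather than counting them as exposed with unknown outcome.

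Section 2.1 makes the safety of berberine relative to rifaximin part of the study aim. Section 2.5 states that participants know their allocation, so the tendency to leave early and silently need not be equal in the two arms. The resulting comparison would be between selected subsets of the exposed patients. Because withdrawn patients are replaced, the loss may also not show in the final group totals.

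**Working it through.** The plan states no adverse event rate and no expected number of withdrawals before week 1, so there is no figure of its own to reproduce. The check is a reading of the rules together, followed by an illustration on assumed counts.

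**Rules side by side, for a patient who takes drug and withdraws on day 3**

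1. Withdrawal on day 3 is permitted (section 2.7).
2. No scheduled adverse event assessment has yet taken place; the first is at week 1 (Table 1).
3. Follow-up stops, so the week 1 and week 2 assessments do not happen (section 2.3.3).
4. If the patient reported an event before leaving (section 2.4.2), safety data exist and the patient stays in the set.
5. If the patient reported nothing, there are no post-dose safety data and the patient is outside the set (section 2.9).

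The gap is therefore confined to dosed patients who withdraw before week 1 and say nothing.

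**Illustration**

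Assumed: 90 dosed in one arm (the recruitment target per group in section 2.6), 8 of them with an adverse event, and k silent early leavers, of whom j had an event.

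- Rate among all dosed: 8/90 = 8.9%.
- Rate under the section 2.9 definition: (8 − j)/(90 − k).

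| k | j | Rate under section 2.9 |
|---|---|---|
| 1 | 1 | 7/89 = 7.9% |
| 3 | 3 | 5/87 = 5.7% |
| 5 | 5 | 3/85 = 3.5% |
| 3 | 0 | 8/87 = 9.2% |

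The first three rows understate the risk; the last slightly overstates it. For scale, the 10% attrition allowance in section 2.6 is 0.10 × 90 = 9 patients per arm over the whole trial. One to five is within that, but nothing in the article says how many would leave before week 1 or how many of those would have had events.

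**What each half of a remedy does (k = 3, j = 3)**

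- Exposure-based set alone, the three counted without an event: 5/90 = 5.6%. This is no closer to 8.9% than 5/87 = 5.7%.
- Exposure-based set with a range for unknown status: 5/90 = 5.6% to (5 + 3)/90 = 8.9%. The range contains the assumed truth.
- Enquiry at withdrawal that reaches all three: 8/90 = 8.9%.

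The enquiry recovers events. The definition keeps every exposed patient in the denominator and makes the remaining unknowns visible.

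**The case against.** The best counter-argument is that the plan already captures most early leavers. Section 2.4.2 asks participants to report any event, and section 2.8 requires losses to be recorded and a monitor's report for each participant that covers adverse events. A patient who says they are stopping because they feel unwell has safety data and is counted. This stands, and it is why the exclusion is a possibility for silent leavers and not a certainty for everyone who stops early. It does not close the gap: spontaneous reporting is not an enquiry, and recording a dropout neither obtains event status nor puts the patient back in the set.

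It is also fair to say that redefining the set alone does not remove the bias, as the arithmetic shows, and that safety is neither the primary nor a listed secondary outcome in section 2.4.1. Both points limit the weight of the concern.

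A reader might go further and infer that the arm with more early stopping will look safer than it is. The article does not support that: direction depends on whether the silent leavers had events, and if they had none the rate rises slightly.

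A reader might also see trouble in the phrase about one kind of drug, or in section 2.7, where for limited symptom response "we will provide alternative interventions including switching medication, probiotics and dietary guidance". Neither adds to the point. Section 2.3.2 gives each participant a single drug, so the phrase naturally means having taken study drug. Section 2.7 does not say that a switch is to the other trial drug, nor when it would occur, and attribution after a switch is detail that an analysis plan may hold.

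**Conclusion.** The point holds in a limited form. The safety set rule in section 2.9, combined with the end of follow-up at withdrawal in section 2.3.3, can exclude dosed patients who leave before week 1 without reporting an event, and in an open-label trial this can happen unequally by arm. It concerns withdrawal from the trial. Section 2.7 ends treatment for severe or unanticipated events and for pregnancy without saying that follow-up ends, so those cases are not caught by this reading.

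The number affected is unknown and probably small. The rates shown rest entirely on assumed counts, and the 5.7% and 9.2% results mark two opposite assumptions about the same three patients. This is a low-cost improvement to the safety analysis, not evidence that the planned comparison is biased in a known direction.

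**What to change.** Make both changes together.

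1. **Section 2.3.3, data collection.** State that at any stop of study drug or withdrawal, unless the patient refuses, one adverse event enquiry is made by the telephone or online route already described, and the answer is recorded on the existing form. This does not alter any treatment rule.
2. **Section 2.9, definition.** Define the safety set as all randomised participants who took at least one dose of study drug. Report by arm the number with no post-dose safety contact, and give a sensitivity range for the adverse event rate, from none of them having an event to all of them having one.

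The cost is one short contact for each of the few early leavers, a changed sentence in section 2.9 and an added one in section 2.3.3. Adverse event rates may come out slightly less favourable, and patients who cannot be reached remain in the denominator with unknown status, which the sensitivity range makes explicit.

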## Abstract

**Introduction:** Small intestinal bacterial overgrowth (SIBO) leads to non-specific abdominal discomfort and nutrient malabsorption. Currently, rifaximin is widely applied in SIBO based on its antibacterial and non-absorbable nature. Berberine is a natural component of many popular medicine plants that ameliorates intestinal inflammation in humans through its modification of the gut microbiota. Potential effect of berberine to the gut may provide therapeutic target for SIBO. We aimed to evaluate the effect of berberine compared with rifaximin on SIBO patients.

**Methods:** This is an investigator-initiated, single-center, open-label, double-arm randomized controlled trial, termed BRIEF-SIBO (Berberine and rifaximin effects for small intestinal bacterial overgrowth). In total, 180 patients will be recruited and allocated to an intervention group (berberine) and a control group (rifaximin). Each participant will receive one 400 mg drug twice a day (800 mg daily) for 2 weeks. The total follow-up period is 6 weeks from the start of medication. The primary outcome is a negative breath test. The secondary outcomes include abdominal symptom relief and alteration in gut microbiota. Efficacy assessment will be performed every 2 weeks, as well as safety assessment during the treatment. The primary hypothesis is that berberine is not inferior to rifaximin for SIBO.

**Discussion:** The BRIEF-SIBO study is the first clinical trial assessing the eradication effects of 2 weeks of berberine treatment in SIBO patients. The effect of berberine will be fully verified by using rifaximin as the positive control. The findings of this study may have implications for the management of SIBO, especially increasing the awareness of both physicians and patients who are suffering from long-term abdominal discomfort and avoiding excessive examination.

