### 2.6 Sample size

We calculated the sample size based on the primary outcome of eradication rate. Gatta and Scarpignato (2017) published a meta-analysis in which the overall eradication rate of rifaximin for SIBO patients according to per-protocol analysis was 72.9%. Therefore, the null hypothesis is postulated to be a rate of 72.9% (*P*
_
*0*
_). We proposed that the effective rate of berberine is 69.8% (*P*
_
*1*
_) (Wang et al., 2002; Chen et al., 2015). Using the non-inferiority design with unilateral *α* = 0.025 and power 1-β = 0.8, 82 participants will be enrolled in each group. However, assuming a 10% attrition rate, we will aim to recruit 90 participants per group.

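### The primary hypothesis is non-inferiority on a binary outcome, but section 2.9 lists only tests of difference at p<0.05, with no margin or confidence-interval rule

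*Protocol article*

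**What the plan says.** - **Hypothesis (Abstract).** "The primary hypothesis is that berberine is not inferior to rifaximin for SIBO".
- **Outcome (section 2.4.1).** "The primary outcome is a negative LHMBT", so each patient is a success or a failure.
- **Design (section 2.6).** "Using the non-inferiority design with unilateral" alpha of "0.025 and power 1-β = 0.8, 82 participants will be enrolled in each group". The rates behind this are rifaximin ("the overall eradication rate of rifaximin for SIBO patients according to per-protocol analysis was 72.9" per cent) and berberine ("We proposed that the effective rate of berberine is 69.8" per cent). No margin is given here or elsewhere in the article.
- **Analysis (section 2.9).** The inferential methods are ANOVA, χ², ANCOVA and Spearman correlation. For categorical data, χ² "tests will examine differences between groups for categorical variables". The threshold sentence begins "Statistical significance was defined as a" and goes on to a p-value below 0.05. The section has no confidence interval for the difference in proportions and no non-inferiority decision rule. The full analysis set (FAS) is the primary efficacy population, the per-protocol set (PPS) is secondary, and missing values are multiply imputed.

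**The concern.** The hypothesis and sample size belong to one framework and the listed analysis to another. A χ² test takes equal proportions as its null. Non-inferiority takes as its null that berberine is worse by at least the margin. Failing to reject equality does not reject that second null, and a small or noisy trial fails to reject equality more easily.

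The trial's one confirmatory conclusion is at stake. The trial is open-label and was still recruiting when the article was submitted. A decision rule written down before the data are analysed is credible in a way that one chosen afterwards is not.

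**Working it through.** **Inputs.** From section 2.6: rifaximin p0 = 0.729, berberine p1 = 0.698, one-sided alpha 0.025, power 0.80, 82 per arm. The article states no margin, so every margin below is an assumption, shown as a range.

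**1. The plan's own figure.** The usual formula is

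n per arm = (z₀.₉₇₅ + z₀.₈₀)² × [p0(1−p0) + p1(1−p1)] / (margin − (p0−p1))².

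The numerator is 7.849 × (0.729×0.271 + 0.698×0.302) = 7.849 × 0.40836 = 3.205, and p0 − p1 = 0.031. Without a margin, 82 cannot be reproduced directly. Solved for the margin:

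margin = 0.031 + √(3.205/82) = 0.031 + 0.198 = 0.229, or about 22.9 points.

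Conversely, the size needed at the stated rates is:

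| Assumed margin (points) | n per arm |
|---|---|
| 10 | 3.205/0.069² → 674 |
| 15 | 3.205/0.119² → 227 |
| 20 | 3.205/0.169² → 113 |
| 23 | 3.205/0.199² → 81 |

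A 20-point margin gives 83 if both arms are set to 69.8% (7.849 × 2 × 0.698 × 0.302 / 0.20² = 82.7). That is close to 82 but does not use the two rates as stated, so 22.9 points is the value implied by the stated inputs and not a documented one.

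**2. What the χ² test does at the plan's assumptions.** All pairs of binomial counts were enumerated at 82 per arm (two-sided 0.05, no continuity correction) with true rates 72.9% and 69.8%:

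- non-significant: 92.8%;
- significant in favour of rifaximin: 6.4%;
- significant in favour of berberine: 0.8%.

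Only the last outcome would by itself imply non-inferiority.

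**3. If non-significance were read as non-inferiority.** This is a conditional calculation. The true deficit is set equal to the margin, so any non-inferiority claim is false. The comparator declares non-inferiority when the lower limit of the Wald 95% confidence interval lies above minus the margin.

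| True deficit = assumed margin (points) | P(χ² non-significant) | False claims, confidence-interval rule |
|---|---|---|
| 10 | 72% | 2.6% |
| 15 | 48% | 2.5% |
| 20 | 24% | 2.5% |
| 22.9 | 14% | 2.3% |

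Halving the information makes this worse: with 41 per arm and a true 20-point deficit, non-significance rises from 24% to 52%.

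**4. One possible result.** Berberine 50/82 and rifaximin 60/82 give a difference of −12.2 points with standard error 7.28, so the 95% confidence interval is −12.2 ± 1.96 × 7.28 = −26.5 to +2.1 points. The χ² p-value is 0.097. The test finds no significant difference, yet the interval fails every margin in the table.

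**5. Power of the confidence-interval rule at 82 per arm, 72.9% vs 69.8%.** About 17% for a margin of 10 points, 39% for 15, 67% for 20 and 81% for 23.

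**The case against.** The strongest reply has four parts.

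- **The χ² test is never expressly tied to the primary outcome.** The sentence is generic, the article condenses a longer protocol, and a confidence-interval rule could sit in a document not shown. The inference must be labelled as such, and it is. But section 2.9 is not silent: it names methods and a threshold, and none of them tests the hypothesis stated in the abstract and section 2.6. That mismatch can be read off the article itself.
- **Nothing says that p above 0.05 will be taken as non-inferiority.** A reader might infer that the plan rewards an inconclusive trial. The article does not support that. It neither states nor rules out such a reading, so the figures in step 3 describe a risk and not a planned rule.
- **The large percentages depend on the margin.** If the margin is about 22.9 points, deficits of 10, 15 or 20 points lie inside it, berberine would truly be non-inferior, and 72%, 48% and 24% would not be false-claim rates. The relevant figure would then be 14%. This stands, and 14% is still well above 2.5%.
- **Rejecting equality can be informative, and p<0.05 need not clash with one-sided 0.025.** A reader might infer that a χ² test can never bear on non-inferiority. That is too strong: a significant result in favour of berberine would imply it at any margin, though with probability 0.8% at the assumed rates. A two-sided 0.05 test also has 0.025 in each tail, so the numerical levels are compatible. The conflict lies in the null hypothesis, not in the alpha.

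**Conclusion.** Wrong as written. Section 2.9 does not carry through the non-inferiority design of the abstract and section 2.6. Taken as it stands, the analysis has a 93% chance, at the plan's own rates and 82 per arm, of a result that says nothing for or against non-inferiority. The false-claim rates (72%, 48%, 24% or 14% at assumed margins of 10, 15, 20 or 22.9 points, against about 2.5%) hold only if a non-significant result is read as non-inferiority and the true deficit equals the margin. The conclusion rests on one inference, that χ² is meant for the primary outcome because no other listed method fits a binary comparison. It does not depend on which margin the sponsor had in mind.

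**What to change.** In section 2.9, replace the χ² test for the primary outcome with the following:

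- Estimate the difference in negative-breath-test proportions, berberine minus rifaximin, with a two-sided 95% confidence interval, pooled over the imputed datasets.
- Declare non-inferiority only if the lower limit lies above minus the margin used for the sample size. State that margin in section 2.6 before analysis.
- Keep the FAS as primary, as now, and report the same analysis in the PPS.
- Test superiority only after non-inferiority has been shown.

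The χ² test can stay for other categorical comparisons.

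**Cost.** A few sentences and no new data, provided that the margin is near 23 points. If the stated margin is smaller, the claim of 80% power must be restated: at 82 per arm it is about 67%, 39% or 17% for margins of 20, 15 or 10 points, and 80% power would need 113, 227 or 674 per arm. Stating the margin would expose that shortfall; the new analysis rule would not cause it.
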